#### WP1B: Population survey

We will use the BiB cohort as a core sampling frame for our longitudinal survey, in addition to surveying members of the general public. Benefits of using the BiB cohort include the detailed longitudinal information available on health and wellbeing for parents and children, existing consent to contact participants, and validated address and email contact details. The survey will measure changes in travel choice behaviour following B-CAP implementation, and attitudes and participants’ views of the intended and unintended impacts of the B-CAP components on health and travel behaviour (see logic model in Supplemental File 1). Given that our research has coincided with the COVID-19 pandemic, we have adapted our planned survey to also include key questions in relation to people’s experiences of the COVID-19 pandemic and subsequent local and national lockdown restrictions. Specifically, items related to health and wellbeing, financial circumstances, changes to transport and travel behaviours and family priorities for healthy and happy children have been added. A copy of the questionnaire can be found in Supplemental File 2.

The population survey will be administered immediately pre, and up to 12-month post implementation of the charging CAZ element of the B-CAP. All BiB families still living within Bradford district will be eligible (~ 10,000, 80% of total cohort). We will offer the survey in a variety of formats including paper based, online, and face to face with multilingual researchers facilitating completion in Urdu, and Mirpuri. The survey will be promoted to eligible families using a variety of well-established recruitment methods, including direct communication (letters in school book bags, post) and wider promotion (social media, website, and newsletters). When the study was originally planned, pre-pandemic, we had aimed to recruit 4000 families (40% response rate). However the COVID-19 pandemic severely curtailed our research activities, and like many other studies we found that participant’s burden increased, impacting on their ability to take part in research. Based on this we revised our estimate to aim for 2000 responses at both time points, and plan to make the survey available to the wider population of Bradford. We will advertise through a variety of online social media channels including and via council communication channels (e.g. email lists, twitter). We will attend community venues and events with computer tablets where participants are able to access the online questionnaire, and paper version of the questionnaire.

#### Analysis methods

In WP1A we will explore the implementation and fidelity of the intervention and determine the extent to which any adaptations affect the functioning principles (described in the logic model) of interventions or their components. For example, assessing categories of ‘what’ (e.g. reduction in numbers of non-compliant vehicles); ‘how’ (e.g. provision of addition public transport infrastructure; incentives schemes to replace vehicles); ‘to whom’ (families/children; business); ‘by whom’ (e.g. council, contractors, public representatives), and whether any (dis) benefits of the intervention are spread equally amongst different socio-economic groups. Qualitative data from the stakeholder interviews, implementation interviews and public focus groups will be analysed separately using thematic analysis [50]. Stakeholder interviews will focus on identifying barriers and facilitators to intervention implementation; the COM-B model [51] will be used as a conceptual model to categorise identified barriers and facilitators. Process implementation data (e.g. documentation forms, meeting minutes) will be reviewed by the project management team, and intervention components categorised into adaptation levels (implemented, not implemented, modified). These will be tabulated, scored and presented descriptively. Documents collected to inform contextual influences will also be analysed using thematic analysis. All forms of implementation and adaptation evaluation data will be used to provide a picture of which (and how) adaptations impacted on which outcomes in relation to the intervention descriptors. Data from our population survey (WP1B) will support an understanding of the mechanisms of any change and will compare travel/air quality attitudes and behaviour pre and post implementation using McNemars test, paired t-test and Wilcoxon signed rank sum test, stratified by participant characteristics such as ethnicity and socio-economic status. We will be able to examine changes for respondents living within and outside CAZ boundaries to explore whether any changes in behaviour or attitudes differ according to proximity to the CAZ boundary. We will combine insights from WP1A and WP1B with relevant data from Bradford Council (e.g. the ANPR survey) to critically review the proposed logic model (see supplemental file); including developing a ‘dark’ logic model [52] outlining key barriers to implementation and threats to the intervention logic to explain any observed unanticipated or adverse events. Results of the implementation evaluation will be considered alongside the evaluation of effectiveness for health outcomes to provide context to help explain findings (including use of implementation data as an effect modifier). This will be done during discussion with the immediate team, wider stakeholders and our community public involvement groups.

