### Aims and objectives

We aim to assess the impact of the B-CAP on attitudinal, behavioural, air pollution and health outcomes, and establish its cost-effectiveness, using a multi-outcome, multi-sector approach. We also aim to explore the factors influencing any impact (or lack thereof) and explore unintended or unanticipated outcomes. The impact of the B-CAP on health inequalities amongst different socio-economic and ethnic groups will be assessed across all outcomes. Our findings will enable the modelling of potential health impacts of a CAZ approach within other cities in the UK and internationally.

Our research questions are as follows:What are the key barriers and enablers to implementation of the B-CAP (including acceptability), and are there unintended consequences of the B-CAP for different stakeholder groups (e.g., increased health and economic inequalities)?Does the B-CAP affect travel choice behaviour and attitudes amongst people who live or work in Bradford at 12 months post implementation?Does the B-CAP reduce exposure to pollution amongst primary school age children up to 12 months post implementation?What is the impact of the B-CAP 3 years post-implementation on:respiratory health (primary outcome, as assessed by weekly counts of respiratory disease related emergency hospital or General Practice [GP] attendance) of children (aged < 18), adults (aged 18-64) and older adults (aged 65+)cardiovascular health (as assessed by weekly counts of cardiovascular disease related emergency hospital/GP attendance) of adults and older adults;birth outcomes such as low birth weight and preterm birth (assessed by monthly counts)How does the B-CAP impact on health inequalities up to 3 years post implementation?What is the value for money of the B-CAP 3 years post-implementation and longer term?

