## Planned intervention- the Bradford Clean Air Plan (B-CAP)

The Bradford Clean Air Plan (B-CAP), which includes a class C charging CAZ was approved by the Government on 12th February 2020 who awarded £43.3 million to Bradford council to implement the plan [36]. We describe the intervention in more detail in Table 2, using the standardised Template for Intervention Description and Replication (TIDierR) checklist [37].

**Table 2 Tab2:** Description of the B-CAP including CAZ using the TIDieR checklist

Brief name	Bradford Clean Air Plan: Breathe Better Bradford
Why	To reduce NO_2_ pollution levels to legal limits (40 μg/m^3^) as quickly as possible. A Class C CAZ will charge non-compliant buses, coaches, heavy goods vehicles, vans, minibuses, taxis and private hire vehicles charged a daily fee to enter the zone. Proposed to instigate desired behavioural responses towards a reduction in most polluting vehicles and an increase public transport use, and active travel. Rigorous modelling (informed by routine monitoring and traffic fleet data) has identified at least 16 core link roads which exceed legal pollution limits, requiring a reduction of 1-18 μg /m3; activities included within the B-CAP have been estimated to achieve up to an 18 μg /m3 reduction in NO_2_ (based on 2018 baseline data). However, it is hoped that the ambitious nature of the plan will mean air quality is improved beyond these limits by harnessing the power of the ‘system’ (e.g. transport, planning, and public health) to work together to further improve outcomes.
What: Materials	Network of 330 automatic number plate recognition cameras, 16 km of digital ducting in 6 new digital rings around the city. A public website contains information for the public and businesses: https://www.bradford.gov.uk/breathe-better-bradford/breathe-better-bradford/

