What: Procedures	The Clean Air Zone is planned to go live in 2022. Daily charges for non-compliant vehicles will be £7 for taxis, £9 for light good vehicles and £50 for heavy goods vehicles. Prior to the go-live date, local businesses and taxi are able to access grants to contribute to the cost of upgrading or replacing their vehicles to CAZ standards with 25% of all grants prioritised for electric vehicles. Exemptions will be provided for local small/medium enterprises (SMEs), schools and charities. The CAZ to be supported by a range of other initiatives including: electric bus routes in key parts of the city with road space allocation to prioritise buses and reduce journey times; installation of alternative energy centres providing cost effective green refuelling/recharging facilities; travel planning with businesses to promote car sharing, active travel and public transport use amongst employees.
Who provides	The intervention is implemented by the Clean Air Plan delivery team within Bradford council. This includes an operations team, grants and business support, monitoring and evaluation, and ultra low emission vehicle programme.
How	Drivers can choose to pay the daily charge up to 7 days before and 7 days after entry. ANPR cameras at CAZ entry points will identify non-compliant vehicles by linking up with the Driver and Vehicle Licensing Agency database. Penalty charge notices will be sent to owners who do not pay within 7 days. Grants and exemptions will be applied for via the Breathe Better Bradford website.
Where	The Clean Air Zone boundary encompassing the city’s inner ring road, and a key corridor out to the North West of the city. It encompasses an area of 22.4 km2, primarily the most deprived inner city wards but including less deprived wards on the outskirts of the city. The boundary contains ~ 20% of the Bradford population.
When and how much	The Clean Air Zone is planned to be live until legal levels of pollution are reached
Tailoring	Clean Air Zone interventions are complex and tailored within each city that they are implemented within.
How well	A number of measures will be used to explore whether the B-CAP is implemented as intended. These will include: fleet composition; number of penalty notices issued; number of vehicles upgraded; number of grants applied for

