## Discussion

We have a rare opportunity to conduct a quasi-experimental evaluation of a city-wide air quality intervention (Bradford Clean Air Plan: B-CAP), which includes implementation of a charging Clean Air Zone (CAZ) to determine its impact on air quality, health outcomes and inequalities across the life-course. Our proposed study is unique in that it additionally includes a full process and implementation evaluation in addition to planned cost-effectiveness analysis. This will provide rich learning to other areas who are planning to implement this type of approach to improve air quality.

The COVID pandemic has been a major challenge to both implementation of B-CAP and the research programme, causing delays in fieldwork and implementation of the B-CAP. Data collection started in Summer 2021 after lock down periods instigated by the pandemic were lifted, approximately 12 months later than planned. However, the corresponding delay in implementation of the plan has meant we have still been able to collected baseline data. We have had to amend our data collection tools and analysis plans to take into account changes in travel behaviour as a result of the pandemic (for example, reduction in travel during initial lockdown periods resulting in improved air quality for a temporary period, decreased use of public transport as lockdown restrictions eased) as well as periods of reduced health service use affecting measurement of our primary outcome. A strength of our study is its use of routinely collected data available from the cBradford dataset which has remained unaffected by the pandemic, and our use of an interrupted time series design with segmented regression break points which means we are able to isolate ‘atypical’ periods during the pandemic lockdown and account for these in our analyses.

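### The paired pre/post tests named for the travel survey cannot separate a B-CAP effect from a background change shared by all respondents, such as pandemic recovery

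*Protocol article*

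**What the plan says.** All references are to the protocol article.

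- **Question.** Aims and objectives asks: "Does the B-CAP affect travel choice behaviour and attitudes amongst people who live or work in Bradford at 12 months post implementation". This is a question about effect.
- **Timing.** WP1B: Population survey states: "The population survey will be administered immediately pre, and up to 12-month post implementation of the charging CAZ element of the B-CAP". Table 2 adds: "The Clean Air Zone is planned to go live in 2022". There are therefore two waves.
- **Tests.** Analysis methods under Work package 1 says the survey data "will compare travel/air quality attitudes and behaviour pre and post implementation using McNemars test, paired t-test and Wilcoxon signed rank sum test", stratified by characteristics such as ethnicity and socio-economic status.
- **Inside and outside.** The next sentence there says change can be examined for respondents within and outside the CAZ, to explore whether it differs by proximity. It names no test.
- **Pandemic.** The Discussion says tools and analysis plans were amended for pandemic travel change, and gives "decreased use of public transport as lockdown restrictions eased" as one example. WP1B says the questionnaire gained "items related to health and wellbeing, financial circumstances, changes to transport and travel behaviours and family priorities".
- **Intended effect.** Table 2 aims at "a reduction in most polluting vehicles and an increase public transport use, and active travel".

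**The concern.** The survey has one measurement on each side of go-live. A paired test on those two waves asks whether behaviour changed, not why. Stratifying by ethnicity or socio-economic status repeats the same question in smaller groups and does not remove a shift that every group shares.

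The article itself identifies a source of such a shift. If public transport use was still depressed at baseline and recovered afterwards, the survey would show a rise of the kind the B-CAP seeks. The survey is meant to inform the mechanism of change and the review of the logic model, so a shared recovery could be read as support for the behavioural pathway.

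The other quantitative packages do address background change. WP2 assesses differences over underlying trends. WP3 adds pandemic change points and a control outcome. WP1B names no equivalent.

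**Working it through.** **The plan's own survey figures.** 80% of 12,500 families = 10,000 eligible, and 40% of 10,000 = 4,000, the pre-pandemic target. Both reproduce. The revised target of 2,000 responses at each time point is a feasibility figure. The article gives no alpha, effect size or discordance for the survey, so there is no survey power figure to reproduce.

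**What each comparison estimates.** Let s be the background change common to everyone, and let b_in and b_out be the B-CAP effects on residents inside and outside the CAZ.

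- Paired change inside = b_in + s; outside = b_out + s. The whole-sample test is a weighted mix of the two, so s stays in it.
- Inside minus outside = b_in - b_out. The common s cancels, but so does any B-CAP effect that reaches both groups equally.

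**Can the WP3 remedy be borrowed?** WP3 handles the pandemic with four segments of a time series. Two survey waves give one difference and cannot support segments.

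**Illustration with no B-CAP effect.** Assumptions, none of them from the article: two-sided alpha 0.05; discordant share q (respondents who change category) of 10-30%; net common shift r of 0-5 percentage points; N = 2,000 pairs. The last is a ceiling, since 2,000 is the target for responses at each wave, not for completed pairs.

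McNemar, normal approximation: reject when the observed net change exceeds c = 1.96 × √(q/N) in absolute value. The standard error of the net change is √((q - r²)/N).

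Example with q = 0.20 and r = 0.02: c = 1.96 × √(0.20/2000) = 0.0196. The standard error is √(0.1996/2000) = 0.00999. (0.0196 - 0.02)/0.00999 = -0.04, so the rejection probability is about 52%.

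| Common shift | q = 10% | q = 20% | q = 30% |
|---|---|---|---|
| 0 points | 5% | 5% | 5% |
| 1 point | 29% | 17% | 13% |
| 2 points | 81% | 52% | 37% |
| 3 points | 99% | 85% | 69% |
| 5 points | 100% | 99.9% | 98% |

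With 1,000 pairs, a 2-point shift gives 52%, 29% and 21%. For a paired t-test with 2,000 pairs, a common shift of 0.05 SD gives 61% and 0.10 SD gives 99%.

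**The inside/outside contrast.** In a simulation of 20,000 runs (2,000 pairs, q = 20%, 20% inside, no B-CAP effect), the difference in change rejected in 4.9-5.2% of runs for common shifts of 0-5 points. The 20% inside is borrowed from Table 2's share of the Bradford population and is an assumption for survey respondents.

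**Its cost in precision**, at 80% power (1.96 + 0.84 = 2.80) and q = 20%:

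- Single-group change: 2.80 × √(0.20/2000) = 2.80 × 0.010 = 2.8 points.
- Inside minus outside: 2.80 × √(0.20 × (1/400 + 1/1600)) = 2.80 × 0.025 = 7.0 points.
- For q from 10% to 30%, the ranges are 2.0-3.4 and 5.0-8.6 points.
- If half the respondents lived inside, the contrast at q = 20% would detect 5.6 points.

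**The case against.** The strongest reply is that the plan already contains the needed comparison. The sentence after the named tests looks at change inside and outside the CAZ, where a common shift cancels. That stands as far as it goes: WP1B is not limited to pre/post change. But the comparison is offered to explore proximity, has no test, and is not made the answer to research question 2. It is also only a partial control. Grants and travel planning are not confined to zone residents, and WP2 expects that benefits may extend past the boundary.

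A second reply is that the survey is exploratory process evaluation, read alongside council camera data, national trends and a critical review of the logic model. The article nowhere says that survey change will be attributed to the B-CAP, as it does say of pollution differences in WP2. This is fair, and it limits the consequence. It does not change the causal wording of research question 2.

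A third reply is that analysis detail belongs in a fuller plan, and that the Discussion reports amended analyses. How COVID items enter a model can indeed be left to such a plan. Here, however, the article does name the tests, and the only analysis amendment it describes is the WP3 segmentation.

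A reader might go further and infer that the survey will credit a post-pandemic rebound to the B-CAP. The documents do not support that:

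- They report no rebound, and give no size or date for one.
- "Data collection started in Summer 2021 after lock down periods instigated by the pandemic were lifted, approximately 12 months later than planned" describes the programme as a whole. The survey baseline is placed immediately before a 2022 go-live, and the fall in public transport use is not dated to it.
- A bias favouring the B-CAP is plausible for public transport use only. The Discussion also cites reduced travel during lockdown, and recovery of car travel would run the other way. For attitudes no direction is established.

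**Conclusion.** The point holds in a limited form. The tests named for WP1B cannot distinguish a B-CAP effect from a change common to all respondents. The article itself names such an influence, and the two elements that could help (the inside/outside comparison and the COVID items) have no stated role in answering research question 2.

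The size is conditional. The 37-81% for a 2-point shift rests on an assumed alpha, shift, discordance and number of pairs. It falls to 21-52% with 1,000 pairs and to the nominal 5% if there is no background change. It shows that a small shared shift would be enough to mislead, not that one occurred. The primary health analysis in WP3 is not affected.

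**What to change.** In Analysis methods under Work package 1:

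1. Report the paired pre/post tests, overall and by stratum, as descriptive change only.
2. Base the answer to research question 2 on the difference in within-person change between respondents inside and outside the CAZ, graded by proximity. Use a regression adjusted for the COVID travel-change items where the questionnaire allows; its content (Supplemental File 2) is not shown, so their suitability needs checking.
3. State that outside respondents are a partial control because B-CAP measures reach beyond the zone, and that a district-wide change cannot be separated from pandemic recovery.

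Restricting the analysis to respondents who say the pandemic did not alter their travel is not advised as the main answer. It selects on recalled behaviour and depends on items not shown.

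The change needs new wording and one regression per outcome, on data already planned. The price is the lower precision shown above (about 7 points against about 3 in the central case) and a more cautious claim.

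### The paired, stratified tests named for the WP1B survey use only two-wave respondents and cannot test whether change differs by CAZ proximity, ethnicity or SES

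*Protocol article*

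**What the plan says.** The analysis methods for Work package 1 name three tests for the WP1B survey, "using McNemars test, paired t-test and Wilcoxon signed rank sum test, stratified by participant characteristics such as ethnicity and socio-economic status". The following sentence says changes will be examined for respondents within and outside the CAZ, "to explore whether any changes in behaviour or attitudes differ according to proximity to the CAZ boundary". It names no method for that comparison.

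The WP1B section describes the sample: "We will use the BiB cohort as a core sampling frame for our longitudinal survey, in addition to surveying members of the general public". For the BiB families it notes "existing consent to contact participants, and validated address and email contact details"; nothing equivalent is stated for public respondents. After the pandemic the target was cut: "we revised our estimate to aim for 2000 responses at both time points, and plan to make the survey available to the wider population". Public recruitment uses social media, council channels and events: "We will attend community venues and events with computer tablets where participants are able to access the online questionnaire". The text does not say whether the 2000 at each wave are the same people, or how public respondents will be linked across waves.

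The Aims and objectives section promises that inequalities by socio-economic and ethnic group will be assessed across all outcomes. For the health outcomes, the Work package 3 analysis methods specify interaction terms as well as stratified analyses. For the survey, only stratification is specified.

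**The concern.** McNemar's test, the paired t-test and the signed-rank test all need both answers from the same person. A plan built on tracked BiB families suits them. A plan widened to people met online or at an event suits them less well, because a person seen at one wave only contributes nothing.

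The second problem remains even with complete pairing. Whether change differs by proximity, ethnicity or SES is a question about a difference in change. A paired test within each stratum asks whether that stratum changed. Setting the results side by side confuses a difference in significance with a difference in effect, and the risk is greatest when the strata differ in size. Table 2 puts about 20% of the Bradford population inside the boundary, so unequal zones are plausible.

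At stake is how the survey's evidence on mechanisms and inequalities is read. A finding that only one zone or group responded could reflect sample size alone.

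**Working it through.** **Figures in the protocol.** 4000 / 10,000 = 40% and 10,000 / 12,500 = 80%, as stated. The revised 2000 is 20% of the 10,000 eligible BiB families if all respondents came from BiB. No power, effect size or number of pairs is given for the survey, so everything below is a scenario.

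**1. Separate tests by zone.** Assumptions: 2000 complete pairs; 20% inside (borrowed from the population share in Table 2), so 400 inside and 1600 outside; an identical true change of 5 points; 20% of pairs discordant; two-sided 5% tests. The standard error of the change is approximately √(0.20/n).

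- Inside: √(0.20/400) = 0.0224; 0.05/0.0224 = 2.24; power = Φ(2.24 − 1.96) ≈ 61%.
- Outside: √(0.20/1600) = 0.0112; 0.05/0.0112 = 4.47; power = Φ(4.47 − 1.96) ≈ 99%.
- Significant outside only: (1 − 0.61) × 0.99 ≈ 39%.

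A direct test of the difference in change has standard error √(0.20/400 + 0.20/1600) = 0.025. It would wrongly declare a difference in 5% of studies, against about 39% from reading the two p-values together.

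**2. Sensitivity to pair count and effect.** Assumptions: continuous outcome, within-person correlation 0.5 (so the SD of change equals the outcome SD), 20% inside, the same true change d in both zones. Power in a zone is Φ(d√n − 1.96). The middle columns give the chance that exactly one zone is significant.

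| Pairs | d = 0.10 SD | d = 0.15 SD | Difference in change detectable with 80% power |
|---|---|---|---|
| 2000 | 48% | 15% | 0.16 SD |
| 1000 | 63% | 44% | 0.22 SD |
| 500 | 51% | 62% | 0.31 SD |

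The size varies, but in every row separate tests disagree far more often than 5% of the time when there is no difference.

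**3. Single-wave responses.** With m pairs out of 2000 responses per wave, paired tests leave out 2(2000 − m) of 4000 responses. At unit variance and correlation ρ, the change has variance 2(1 − ρ)/m from pairs and 2/(2000 − m) from single-wave responses; an all-responses estimate combines the two by inverse variance.

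- m = 2000: nothing is left out.
- m = 1000, ρ = 0.5: 50% left out; variance 0.00100 paired only, 0.00067 with all responses (33% lower).
- m = 500, ρ = 0.5: 75% left out; variance 0.0020 against 0.0008 (60% lower).

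For ρ = 0.3, 0.5 and 0.7, the ratio of paired-only to all-responses variance is 1.7, 1.5 and 1.3 with 1000 pairs, and 3.1, 2.5 and 1.9 with 500. These gains assume that single-wave respondents at the two waves come from the same population.

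Steps 1 and 3 are separate illustrations: step 1 uses 2000 complete pairs, at which step 3 shows no loss.

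**The case against.** A reader might infer that the inside-versus-outside comparison is never made. The text does not support that: the comparison is a stated aim, and only a method able to carry it out is missing. Nor does the protocol say that zones will be judged by comparing p-values; the word stratified is attached to ethnicity and SES. A condensed article may leave the test for an exploratory contrast to a fuller plan. Even so, the tests it does name cannot answer the question, and the same article specifies interaction terms for the health outcomes.

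A reader might also infer that many responses will be discarded. That is not established. The survey is called longitudinal, BiB is the core frame, and BiB families can be re-contacted. Nothing says public respondents cannot be. The loss could be zero, and paired tests are valid for people who answer twice.

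Pooling everyone is not plainly better either. People recruited by convenience at one wave were not necessarily missing from the other, and a shift in who is recruited could look like a change in behaviour. Paired tests avoid that. This stands, and is why the all-responses model is proposed only as support.

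Nor should a wave by zone term replace the overall comparison. Research question 2 covers people who live or work in Bradford, and the Work package 2 analysis methods accept that benefits may extend beyond the boundary.

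Finally, a pre/post change may include travel recovering after lockdown. The protocol recognises this: pandemic travel items were added to the survey and the Discussion says analysis plans were amended. These are not a comparator, but the issue was not overlooked.

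**Conclusion.** The point holds in limited form. The named tests cannot use a single-wave response, and none of them tests whether change differs by zone, ethnicity or SES. The first limitation matters in proportion to the number of unlinked respondents, which is unknown. The second applies however many pairs there are.

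In the binary scenario, a spurious significant-outside-only result arises in about 39% of studies; in the continuous scenarios, exactly one zone is significant in 15% to 63%. The correlation, effect sizes, discordance and pair counts are assumptions. The 20% share inside is the district's population share, which the survey sample need not match. The direction of the problem does not depend on these exact values.

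The survey serves the process evaluation. The WP3A primary outcome is unaffected.

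**What to change.** - Keep the overall paired pre/post comparison among linked respondents.
- Replace any comparison of separate stratum tests with a direct test of difference in change: a mixed or GEE model with wave, zone (within/outside, as the survey plan has it), wave by zone, wave by ethnicity and wave by SES terms.
- Record a linkage identifier and recruitment source (BiB or public) at both waves, and state whether 2000 means pairs or responses per wave.
- Add an all-responses version of the model, adjusted for recruitment source and demographics, as a supporting analysis.

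The cost is analysis wording plus two recorded items. The all-responses version assumes data missing at random given the covariates and no unmeasured shift in who is recruited between waves. Interaction tests have limited precision: in the continuous scenario, 1000 pairs detect a difference in change of 0.22 SD with 80% power. The report should also say that a null wave by zone term does not show absence of a district-wide effect.
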